**c**. **For babies with surgical conditions born in England**

The long-term outcomes and academic attainment of the approximately 8000 children who have undergone early childhood surgery will be investigated, and factors associated with educational attainment identified. The primary outcome will be attainment of a Good Level of Development (GLD) on the Early Years Foundation Stage Profile (EYFSP). Secondary outcomes will include mortality, hospital admissions, school absence and special educational needs status. We will perform multiple linear regression for covariates with continuous outcomes and logistic regression for dichotomous outcomes, to analyse the contribution of various determinants on the development of outcomes.

**Aim two**: **to evaluate the impact of neonatal interventions on the later health and educational outcomes of very preterm babies using an exemplar intervention: fortification of human breast milk versus no fortification**

The utility of the linked dataset generated will be tested, aiming to address one of the top priorities for preterm babies, whether fortification of breast milk (versus no fortification) affects key long-term outcomes for very preterm babies.

Only babies who achieve full enteral feeds (defined as three consecutive days with enteral feed given without an intravenous fluid or parenteral nutrition) will be included. Only babies old enough to have an Early Years Foundation Stage Profile (i.e. age five) will be included. Babies with major congenital malformations (likely to influence feeding strategies, and/or require surgery in the neonatal period) will be excluded. Babies who received management for necrotising enterocolitis prior to attaining full enteral feeds will be excluded.

Babies will be grouped by whether they receive breast milk fortifier during their neonatal admission, and those who do not.

The primary outcomes of interest will be attainment of a Good Level of Development on the Early Years Foundation Stage Profile (EYFSP). Secondary outcomes will include: Special Educational Needs provision, diagnosis of developmental delay, diagnosis of Autism, diagnosis of attention deficit hyperactivity disorder, mortality, diagnosis of necrotising enterocolitis requiring surgery or causing death.

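### Aim two's eligibility rules do not require human milk, so exclusively formula-fed babies can enter the unfortified group unless milk type is in the propensity model, which the plan does not commit to

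*Protocol article*

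**What the plan says.** All of this is in the protocol article, under How NeoWONDER will address its aims, Aim two.

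- **Question:** "whether fortification of breast milk (versus no fortification) affects key long-term outcomes for very preterm babies". The Aims section also names the intervention as fortification of human breast milk.
- **Feeding criterion:** "Only babies who achieve full enteral feeds (defined as three consecutive days with enteral feed given without an intravenous fluid or parenteral nutrition"). The definition turns on the absence of intravenous fluid and parenteral nutrition; the kind of milk is not mentioned.
- **Other criteria:** the child must have reached the age of the school assessment; "Babies with major congenital malformations (likely to influence feeding strategies, and/or require surgery in the neonatal period) will be excluded"; and necrotising enterocolitis that was managed before full feeds is a further reason for exclusion. None of these concerns milk type.
- **Exposure groups:** "Babies will be grouped by whether they receive breast milk fortifier during their neonatal admission, and those who do not".
- **Primary outcome:** attainment of a Good Level of Development, abbreviated GLD below, on the school-entry profile.
- **Adjustment:** the next paragraph leaves the propensity variables to a causal graph. It names birth year, gestation and birth-weight-for-gestation decile for close matching, and applies callipers to the remaining variables to bring standardised differences under 0.1. It discards observations off common support and ends with an outcome regression on the matching variables. Milk type is not named at any of these steps.

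**The concern.** The question defines a population: babies who received human milk that either was or was not fortified. The rules define a wider one. A baby fed only formula passes every criterion and can be assigned only to the group without fortifier. That baby's probability of exposure is zero by construction, which is a structural positivity problem, and the baby cannot inform the question asked.

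If such babies stay in the matched comparator, the estimate mixes two contrasts: fortified versus unfortified human milk, and human milk versus formula. The second brings in the family and socioeconomic circumstances that go with feeding, which plausibly relate to school attainment. Milk type plausibly also relates to the necrotising enterocolitis secondary outcome. A difference between groups could then not be credited to fortifier, and a large cohort would make the mixed estimate look precise without making it less mixed.

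**Working it through.** The article gives no sample size, effect size or expected GLD rate for Aim two, so there is no planned figure to reproduce. The check has three parts.

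**1. Trace one baby through the rules.** Take a very preterm baby fed only formula, old enough for the school assessment, with no major malformation and no early necrotising enterocolitis.

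| Rule | Result |
|---|---|
| Full enteral feeds | met; milk type not specified |
| Age criterion | met |
| Two exclusions | neither applies |
| Grouping by fortifier | unfortified group |
| Close matching on the three named variables | does not act on milk type |
| Common-support discard | acts on milk type only if it is in the model |

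**2. What the matching rules would do in each case.**

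- *Milk type omitted.* A formula-fed baby can have an ordinary propensity score and match well on gestation and birth weight. Balance checks on the included covariates would not show the problem.
- *Milk type included.* Suppose an indicator for exclusive formula feeding is among the balanced covariates, and the standardised difference uses the average variance of the two groups (an assumption). The exposed group has share 0 and the matched comparators share q, so the difference is q / √(q(1 − q)/2). Setting this at 0.1 gives q/(1 − q) = 0.1²/2 = 0.005, so q = 0.005/1.005, about 0.5%. Meeting the plan's own target would then leave almost none of these babies.

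The outcome therefore depends on one modelling decision that the article leaves open.

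**3. Possible size if milk type is omitted.** Every input here is assumed: a true fortifier effect of zero, a share q of the comparator fed only formula, and GLD lower by d percentage points in those babies. The spurious risk difference, in favour of fortifier, is q × d.

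| q | d = 3 | d = 5 | d = 10 |
|---|---|---|---|
| 10% | 0.3 | 0.5 | 1.0 |
| 20% | 0.6 | 1.0 | 2.0 |
| 40% | 1.2 | 2.0 | 4.0 |

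For scale, with an assumed 10,000 matched pairs and GLD near 50%, and treating the groups as independent, the 95% half-width is 1.96 × √(2 × 0.25/10,000) = 0.0139, or 1.39 points. Three of the nine cells exceed it.

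With an assumed 5,000 per group, 50% GLD in human-milk-fed babies and a two-sided 5% test, the chance of a significant result favouring fortifier when it has no effect is:

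- about 17% at q = 20%, d = 5;
- about 52% at q = 20%, d = 10;
- about 85% at q = 30%, d = 10.

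These are crude mixture figures. They apply no matching, trimming or covariate adjustment, so q and d should be read as whatever remains after those steps.

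**The case against.** The strongest reply is that the plan already contains the remedy. Milk type is an obvious determinant of receiving breast milk fortifier, so a sensible causal graph would include it. Exclusively formula-fed babies would then have a propensity near zero, and the common-support rule, a standard response to non-positivity, would drop them. This stands as a possibility, and it rules out the inference that nothing in the plan could remove these babies. It does not settle the matter, because the text never says that milk type is in the model. If it is, the model is doing the work of an eligibility rule.

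A second reply is that the question itself implies breast milk in both groups, and that a condensed article may leave out a feeding-data filter. This has some force. But the article does list the Aim two criteria, down to a three-day definition of full feeds, and it states the grouping rule. Followed as written, these give a comparator wider than the question.

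A third reply is that the illustrative sizes rest wholly on assumptions and ignore the adjustment. That is correct, and it limits what can be claimed about magnitude.

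**Conclusion.** The point holds in a conditional form. As written, the Aim two eligibility and grouping rules admit exclusively formula-fed babies to the unfortified group. Whether they stay in the matched comparison depends on whether milk type enters the propensity model, which the article does not fix. If it does not enter, the contrast is partly human milk versus formula, with the associated family confounding.

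A reader might infer that the estimate will certainly be biased, and by more than its sampling error. The documents do not support that. They give neither the formula-only share, nor the GLD gap, nor the matched sample size. On assumed values the unadjusted bias is 0.3 to 4.0 points, and six of the nine combinations lie within the 1.39-point half-width, itself based on assumed numbers. The direction, favouring fortifier, also rests on the assumption that formula-fed babies do worse on GLD.

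The problem is confined to babies fed formula alone; mixed-fed babies can receive fortifier. It still deserves correction before analysis, because it affects the primary contrast of Aim two and is cheap to remove.

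**What to change.** 1. In the Aim two eligibility text, limit both groups to babies with any recorded human milk, mother's own or donor, up to the end of the three-day period that defines full enteral feeds. Measure it the same way in both groups, and apply it before the propensity model is fitted.
2. In the propensity paragraph, state that the share of feed days with human milk up to that same point is in the propensity model and in the balance checks.
3. Add a sensitivity analysis that defines eligibility by any human milk during the neonatal admission.

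Human milk should not be required on the three qualifying days themselves. Exposure is defined over the whole admission, and that stricter rule would drop babies who had human milk, and possibly fortifier, at other times.

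The cost is two or three sentences and a filter on neonatal feeding data. The comparator group becomes smaller. Most of those removed cannot inform the question, but a few babies whose human milk began only after full feeds are also lost; the sensitivity analysis covers these. Where fortifier starts before the three-day period ends, the human-milk share is measured partly after exposure, and the report should say so.

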**a**. **For very preterm babies born and cared for in England**

The health outcomes of the approximately 102,000 very preterm babies included in cohort one, and the education outcomes for the approximately 80,000 very preterm babies in cohort two will be described. The health outcomes of interest include mental health and behavioural conditions, and health resource use and a health economic evaluation. These outcomes are detailed in S4 File. The education outcomes of interest include school attendance rates, special school attendances rates, statement of educational needs, and educational attainment: at Early Years Foundation Stage (age four years), Key Stage one (age seven years), and Key stage two (age 11 years).

Descriptive analyses will be undertaken on the linked datasets, with important consideration given to data quality and completeness. We will describe the characteristics of admission to neonatal care and subsequent readmissions including length of stay, interventions or procedures and healthcare resource use during the neonatal stay.

We will determine mortality rates and causes of death following discharge, and investigate the risk of admission to paediatric care. We will determine the potential modifying impact of socioeconomic factors on long-term physical health outcomes. To explore the timing of readmission and determine whether there is correlation with diagnoses or demographics, survival analysis approaches such as Cox regression or flexible parametric modelling will be used. The absolute mortality rates and hazard ratios will be reported with 95% confidence intervals. A logistic regression will be undertaken to determine the odds ratio (with 95% confidence intervals) of outcomes of interest (amongst the included population) at predefined ages during the study follow-up period. Subgroup analyses will be undertaken to examine geographic variation, temporal trends, and trends by gender.

We will explore trends in education outcomes (outlined above) for the following subgroups: geographic variation (area of birth); temporal trends (year of birth); eligibility for free school meals; looked after child; first language spoken at home; school type (mainstream or special school); by school ages.

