Characteristics for the two groups will be described. A propensity model will be developed using a direct acyclic graph to inform the variables included. Missing variables will be described, and strategies developed to address them. Dependant on findings, this may include use of ‘missing’ categories for missing categorical variables, and use of multiple imputation by chained equations. Nearest neighbour matching will be used, with callipers applied to limit the distance between pairs for both specific variables and overall propensity score. Callipers will additionally be set to ensure close matching of the following specific variables: birth year, birth weight decile for gestation, and gestation. For remaining variables, callipers will be applied to achieve absolute standardised mean differences below 0.1. Observations outside the common support will be discarded. The matching ratio will be optimised based on group sizes. Covariate balance will be assessed, with absolute standardised mean differences and Kolmogorov-Smirnov statistics examined for all covariates. Distributions of propensity scores between the two exposure groups were compared before and after adjustment using density estimates. Balance plots will be produced for all variables, using density estimates for continuous variables and histograms for categorical variables. A weighted regression model conditioned on the variables included in matching will be used to give an estimate for each outcome.

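### Aim two assigns fortifier groups over the whole neonatal admission, so deaths before a later start count as unfortified and the mortality comparison is biased towards fortification

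*Protocol article*

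**What the plan says.** All of this is in the protocol article, under How NeoWONDER will address its aims, Aim two.

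- **Entry** (the condition for being in the comparison): "Only babies who achieve full enteral feeds (defined as three consecutive days with enteral feed given without an intravenous fluid or parenteral nutrition) will be".
- **Exclusion:** "Babies who received management for necrotising enterocolitis prior to attaining full enteral feeds will be excluded". Neither entry rule refers to when fortifier began.
- **Exposure:** "Babies will be grouped by whether they receive breast milk fortifier during their neonatal admission, and those who do not". Classification therefore stays open until discharge or death.
- **Primary outcome:** "The primary outcomes of interest will be attainment of a Good Level of Development on the Early Years Foundation Stage Profile (EYFSP").
- **Secondary outcomes** include "mortality, diagnosis of necrotising enterocolitis requiring surgery or causing death".
- **Adjustment:** propensity matching, with extra callipers on "birth year, birth weight decile for gestation, and gestation", followed by one model per outcome: "A weighted regression model conditioned on the variables included in matching will be used to give an estimate for each outcome".

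For Aim two the article states no start of follow-up, no exposure window that closes before outcomes are counted, no landmark and no time-varying exposure. Survival models (Cox or flexible parametric) appear only under Aim one, for the timing of readmission.

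**The concern.** Entry and exposure are fixed at different times. A baby enters on reaching full feeds, but the group is known only by looking ahead to discharge. Any baby who starts fortifier after full feeds must have survived to start, so deaths in that interval can fall only in the unfortified group. This is immortal time. Matching balances characteristics measured at baseline; it cannot balance a grouping that depends partly on surviving long enough to be exposed.

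A second, separate issue concerns babies who start fortifier before full feeds. If fortifier caused NEC or feeding failure in that period, the affected babies would be removed by the entry rules, and the harm with them.

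Aim two is the programme's exemplar evaluation of a neonatal intervention. It draws on a cohort of about 80,000 before its own restrictions ("the education outcomes for the approximately 80,000 very preterm babies in cohort two will be described"). Size does not help: a large sample gives a narrow interval around a biased estimate.

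**Working it through.** The article gives no event rate, effect size or fortifier timing for Aim two, so there is no planned figure to reproduce. The check asks what the stated grouping returns when fortifier truly has no effect.

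**Assumed inputs (none is in the article).** A share p of babies is destined for fortifier, independently of risk. Start is exponential with mean m days after full feeds. The event risk after full feeds is r = 3%, with a hazard declining on a time constant of τ = 20 days. Discharge is at L = 50 days. Fortifier is not started after an event, which is exact for death.

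**Share of events that precede the planned start:**
q = [(1/τ) / (1/τ + 1/m)] × [1 − exp(−L(1/τ + 1/m))] / [1 − exp(−L/τ)]

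**Risks under the plan's grouping,** with s = 1 − exp(−L/m) the share of event-free destined babies who start before discharge:
- Fortified: p·r·(1−q) / [p(1−r)s + p·r·(1−q)]
- Unfortified: [(1−p)r + p·r·q] / [1 − fortified denominator]

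**Example, p = 0.5 and m = 5.** q = 0.2 × 1.000 / 0.918 = 0.218. Fortified: 0.01173 / 0.4967 = 2.36%. Unfortified: 0.01827 / 0.5033 = 3.63%. The apparent risk ratio (RR) is 0.65; the true RR is 1.

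| Mean start after full feeds | p = 20% | p = 50% | p = 80% |
|---|---|---|---|
| 2 days | 0.88 | 0.82 | 0.66 |
| 5 days | 0.75 | 0.65 | 0.43 |
| 10 days | 0.60 | 0.48 | 0.28 |

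Simulation with 4 million babies per scenario agrees to within 0.02. With m = 5 and p = 0.5, τ of 7 or 60 days gives 0.42 or 0.77. Varying r from 1% to 6% leaves the RR at 0.64-0.66.

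**A second set of assumptions** (40-80% destined, median start 3-14 days after full feeds, risk 2-4%, mean event time 14-28 days) gave 0.21 to 0.81 by simulation. Its central case (60%, 7 days, 4%, 14 days) gave 0.39. By hand, ignoring discharge, q = (1/14) / (1/14 + 0.0990) = 0.419 and the risks are 2.36% and 6.35%, RR 0.37.

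**Starts before full feeds.** These babies contribute no immortal time after entry, so q is multiplied by the share that starts later. With m = 5 and p = 0.5, early shares of 25%, 50%, 75% and 100% give RR 0.73, 0.81, 0.90 and 1.00.

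**NEC survivors fortified later.** Under the plan's wording they count as fortified. If 25-100% of them are, the simulated NEC RR is 0.69-0.86, while the death RR stays at about 0.65.

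**Entry rules alone.** Under a true null they give RR 1.0. Now let fortifier double the NEC hazard only before full feeds, with all starts in that period and a cumulative hazard of 0.03 before and 0.03 after. Counting everything, RR = (1 − e^−0.09) / (1 − e^−0.06) = 8.61% / 5.82% = 1.48. After the exclusion both groups have 1 − e^−0.03 = 2.96%, RR 1.00. With strong frailty, simulation moves 1.41 to 0.91. With half starting early (no frailty), so that both mechanisms act, 1.24 becomes 0.80.

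**Effect of alignment.** On null data, classifying by fortifier status at 3, 7 or 14 days after full feeds, among babies still event-free, gives RR 0.99, 1.01 and 0.99.

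**The case against.** The case for leaving the plan alone has several parts.

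- **The affected outcomes are secondary.** This stands. Good Level of Development is assessed at about age five, long after the exposure window closes. A reader might infer that the primary comparison is materially distorted, but nothing in the article supports that. If every early event is fatal, the misplaced babies are never assessed; a check with frailty acting on both death and attainment gave 50.4% against 50.4%. If every event is non-fatal and blocks later fortifier, the central case puts 6.35 − 2.36 = 4.0 percentage points more events in the unfortified group. If attainment in those babies is 10, 20 or 40 points lower (assumed), the groups differ by 0.4, 0.8 or 1.6 points. This takes deaths as unassessed rather than as failures, which the article does not specify.
- **NEC before fortifier does not always count as unfortified.** This stands, and is why the direction is firmer for death.
- **The NEC exclusion does not itself create apparent benefit.** This also stands. A reader might infer that both mechanisms bias a true null; only immortal time does. The exclusion hides early harm if there is any.
- **The low risk ratios follow from the chosen timing.** This stands. Scenarios in which all starts follow full feeds cannot be read as an estimate of the bias, so the range has to extend to 1.0.
- **A journal article condenses a fuller plan.** This stands for covariate timing and follow-up detail: the article does not say covariates are measured after exposure, and they are chosen from a causal diagram. It does not rescue the exposure rule, which is stated outright and would conflict with any later time zero.

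**Conclusion.** The point holds for mortality and, less firmly, for surgical or fatal NEC. Followed as written, the grouping rule biases these comparisons towards fortification under a true null, unless every fortified baby starts by full feeds. The article does not require that.

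The size cannot be determined from the article. Under the assumptions shown, the apparent null RR ranges from about 0.2-0.3 to 1.0. The bias is a direction and not a guarantee of apparent benefit: with a constant true hazard ratio of 1.5 and half starting early, an aligned RR of 1.45 shows as 1.22. Confounding by indication could add bias either way.

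The hiding of early harm by the entry rules is a separate point and depends on such harm existing. The primary outcome is affected at most indirectly. Because the directly affected outcomes are secondary and the timing is unknown, this is something that should be fixed rather than a flaw that invalidates Aim two.

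**What to change.** For mortality and NEC in Aim two:

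1. State a time zero, for example the third day of full enteral feeds.
2. Compare fortifier strategies from that time with a grace period (clone-censor-weighting), or treat fortifier as a time-varying exposure. A landmark analysis is a simple alternative.
3. Count only outcomes after time zero, or after the landmark.
4. Measure all matching covariates at or before time zero.
5. Say how babies fortified before time zero are handled: either exclude them as prevalent users, or move time zero to first eligibility for fortifier. In either case, eligibility exclusions should not depend on events after exposure.

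No new recruitment is needed. The cost is plan wording and more programming, and it depends on start dates being available in the neonatal care data to be extracted.

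A landmark has a further price. At day 7 it drops 1 − e^(−7/28) = 22% of events if the mean event time is 28 days, or 1 − e^(−7/14) = 39% if it is 14 days (both assumed). If the median start were 14 days, only 1 − 2^(−7/14) = 29% of fortified babies would have started by day 7. The other 71% would be classed as unfortified, which dilutes any real effect. The landmark should therefore be chosen from the observed start times, before outcomes are examined.
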